### Neuroimaging analysis

Task-based fMRI data will be pre-processed using Statistical Parametric Mapping (SPM12; Wellcome Trust Centre for Neuroimaging, London, UK), implemented in Matlab R2019b (MathWorks, Natick, MA, USA). Pre-processing will include realignment, slice-time correction, co-registration to the skull-stripped structural image, normalisation, and smoothing with a 6 mm FWHM Gaussian kernel. To remove low frequency noise from pre-processed data, a high-pass filter will be applied using SPM12’s default settings. For all first-level analyses, data will be analysed using a general linear model that models the time-series as a sequence of events convolved with the canonical hemodynamic response function provided by SPM12. We will analyse physiological data using either the CompCor [37] or RETROICOR approach, implemented in the TAPAS toolbox [38]. We will use the Computational Anatomy Toolbox (CAT12.8, [39]) for segmentation of T1 images.

### Are different brain regions involved in event-based vs. time-based prospective memory?

We will first analyse which brain regions are involved in event-based vs. time-based prospective memory. For the first-level analysis, we will fit one model for each prospective memory task. Each model will include three regressors, the first for ongoing trials during the ongoing task only block, the second for ongoing trials during the prospective memory block, and the third for prospective memory trials. We will build regressors using the onset of every correct answer. Task instructions will be modelled as regressors of no interest. We will define different contrasts corresponding to different prospective memory phases: 1) to obtain brain activity that is associated with maintenance of an intention, we will create contrasts between ongoing trials during the prospective memory block vs. ongoing only trials, 2) to obtain brain activity corresponding to the detection of a target, retrieval of an intention and its’ execution, we will create contrasts between prospective memory trials vs. ongoing trials during the prospective memory block. For time-monitoring, we will fit a model with the number of clock checks during the different time intervals previously described in the behavioural analysis. The onset will be defined as the moment in which the participant presses the key to check the clock. For time-monitoring, we will define contrasts between the different time intervals such as: T-15 vs. T-30, T-15 vs. T + 15, T-15 vs. T + 30, T-30 vs. T + 15, T-30 vs. T + 30, T + 15 vs. T + 30. Again, we will include six nuisance regressors for the six movement parameters as well as regressors of physiological data.

For second-level analyses, we will first use paired t-tests on first-level contrasts in the control group to test whether there would be differences in brain activity when comparing event-based to time-based prospective memory. Then, conjunction analysis will be performed to discern the neural substrates that are common in both task types. Then, we will calculate brain-behaviour correlations using beta estimates from significant regions correlated with task performance.

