### Prospective memory task

To examine the neural substrates of event-based and time-based prospective memory, we will use a computerized task in the MR scanner [32], which will be presented with PsychoPy (v2021.1.2). The task will consist of four blocks: During the first and the third block, participants will perform a 1-back working memory task (as an ongoing-task), during which they will need to decide whether the current image is the same as the image presented just before (Fig. 2). Pseudorandom sequences of 238 Snodgrass & Vanderwart [33] pictures will be displayed on a screen for 2–3 s, followed by a 1–2 s inter-stimulus interval, used as a temporal jitter. During the second and the fourth block, a prospective memory task will be added to the ongoing task. One block will contain the event-based task and the other block the time-based task. The order will be counterbalanced across participants. In the event-based task, participants are asked to press a button whenever an animal appears on the screen (Fig. 2). Every answer that occurs within 5 s following the presentation of an animal will be considered as a prospective memory hit [32, 34]. In the time-based task, participants are asked to press a button whenever one minute has passed (Fig. 2). To monitor the time, they will be able to press another key to display a clock for 3 s in the upper left corner of the screen. Every correct response occurring ± 2.5 s around each target time will be counted as a prospective memory hit [32, 34]. Each prospective memory block will consist of 158 trials; out of these, 54 trials will be ongoing 1-back hits (i.e., trials in which the picture will be identical to the previous one), and 10 prospective memory cues (i.e., one every minute at 1:00, 2:00, 3:00… until 10:00) so that both tasks are similar. Each prospective memory block will last 10.5 min.

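### The event-based retrieval contrast sets cue pictures that are never immediate repeats against ongoing trials of which about 36% are, so it mixes repetition and match-decision effects with retrieval

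*Protocol article*

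**What the plan says.** The section of the protocol article headed 'Prospective memory task' gives both prospective memory blocks the same make-up: "Each prospective memory block will consist of 158 trials; out of these, 54 trials will be ongoing 1-back hits", defined as "trials in which the picture will be identical to the previous one", together with "10 prospective memory cues" placed at each full minute from the first to the tenth. In the event-based task "participants are asked to press a button whenever an animal appears on the screen", so every animal is a cue. In the time-based task "participants are asked to press a button whenever one minute has passed", so the response is tied to elapsed time and not to a type of picture.

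The section on brain regions in event-based versus time-based prospective memory then fixes the first-level model. It has three regressors. The first is for the ongoing-only block, and the other two are "the second for ongoing trials during the prospective memory block, and the third for prospective memory trials". Events are placed at correct answers. The retrieval contrast is described thus: "we will create contrasts between prospective memory trials vs. ongoing trials during the prospective memory block". At the second level, event-based and time-based contrasts are compared by paired t-test in the control group. A conjunction analysis and brain-behaviour correlations follow. Nothing in the model separates ongoing trials that repeat the previous picture from those that do not.

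**The concern.** A contrast isolates retrieval only if the trials on its two sides are alike in everything else that drives the signal. Here they differ in a known property of the stimulus. Event-based cues are always a change of picture. More than a third of the ongoing trials subtracted from them are the same picture shown again, with a different 1-back decision. Any response to repetition, or to deciding 'same' rather than 'different', goes into the event-based retrieval map and is read there as detection or retrieval of an intention.

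At stake is the first aim, the functional anatomy of prospective memory. The event-based map feeds the paired comparison with the time-based task, the conjunction and the brain-behaviour correlations. The authors expect the two tasks to differ, so a difference that comes from stimulus composition could be taken as support for that expectation.

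**Working it through.** **Inputs from the article.** 158 trials per prospective memory block; 54 immediate repeats; 10 cues, one per minute; pictures shown for 2 to 3 s plus a 1 to 2 s interval; block length 10.5 min; one pooled ongoing regressor; time-based hit window ±2.5 s.

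**1. Is 158 the whole block?** Taking mid-range timings (assumption), a trial lasts 2.5 + 1.5 = 4 s. Then 158 × 4 = 632 s, and 632 / 60 = 10.53 min, which reproduces the stated 10.5 min. If the cues came on top of the 158, 168 × 4 / 60 = 11.2 min, which does not fit. The cues are therefore counted within the 158.

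**2. Share of repeats among ongoing trials.**
- Ongoing trials: 158 - 10 = 148.
- Repeats: 54 / 148 = 36.5%.
- Non-repeats: 148 - 54 = 94.

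**3. Can an event-based cue be an immediate repeat?** The picture before it would have to be the same animal, and so a cue itself, about 4 s earlier. That contradicts one cue per minute. The share of repeats among event-based cues is therefore 0. This agrees with the article listing cues separately from the ongoing 1-back hits.

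**4. Net repetition weight of a retrieval contrast** = share of repeats in prospective memory trials minus share in ongoing trials. For the event-based task: 0 - 0.365 = -0.365.

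**5. Presented versus modelled trials.** Regressors contain correct answers only, so 36.5% is the share presented and not the share modelled. For illustration, with 70% accuracy on matches and 95% on non-matches (assumed), 54 × 0.70 = 37.8 and 94 × 0.95 = 89.3, giving 37.8 / 127.1 = 29.7%. If only matches call for a press, which the article does not settle, the ongoing regressor would consist wholly of repeats.

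**6. Event minus time.** Let p be the share of repeats among pictures on screen at time-based presses. The difference is (0 - 0.365) - (p - 0.365) = -p. The ongoing mix is the same in both blocks and cancels.
- Presses on unconstrained pictures: p = 54 / 158 = 0.342, so the imbalance is about -0.34.
- Target-time pictures all non-repeats: p = 0, so the paired difference is unaffected, but both retrieval maps carry -0.365.

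**7. Precision after splitting.** Treating single-trial responses as independent with equal variance, and all answers as correct, the contrast variance goes from 1/10 + 1/148 = 0.1068 to 1/10 + 1/94 = 0.1106. The ratio is 1.036, so the standard error rises by about 1.8%.

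**The case against.** The strongest case on the other side concerns the comparison between tasks. A reader might infer that the 36% biases the event-versus-time result directly. It does not. Both blocks have the same ongoing mix, which drops out of the paired difference. What remains depends on the pictures at time-based presses, and the article does not specify them. Reading cues and repeats as mutually exclusive at target times in both blocks would put the paired bias at about 0. Against that, the time-based response is not tied to a picture, the hit window is 5 s wide against a mean trial of about 4 s, and no constraint on pictures around target times is stated. Neither reading is certain, so this consequence must stay conditional.

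A reader might also infer that cue pictures never recur anywhere in the task. The text supports only that they are never immediate repeats, which is all the argument needs. Nor does the document supply a size for repetition effects. A percentage bias would need an outside assumption about how much a repeated picture lowers the response, and the 'same' decision need not act in the same direction.

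The reach is limited too. The primary outcomes are behavioural. The incentive-versus-control imaging tests compare the same contrast with the same task composition in both groups, so a constant imbalance largely cancels. For the maintenance contrast no imbalance is shown, because the match share of the ongoing-only block is not given.

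All of this stands as a limit on scope. None of it removes the imbalance in the event-based retrieval contrast, which follows from the stated design and the stated model.

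**Conclusion.** The point holds for the event-based retrieval map. As written, that contrast has a net repetition weight of about -0.36 on presented trials, with the modelled share depending on accuracy and on the response rule. It cannot separate retrieval from picture repetition and the match decision. The sign and size of the effect in any region are not derivable from the document.

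For the event-versus-time test the point is conditional: an imbalance of about -0.34 if time-based presses fall on unconstrained pictures, and none if target-time pictures are all non-repeats. In the latter case both retrieval maps share the flaw, so at least one first-aim result is affected under either reading. This is a worthwhile, inexpensive improvement to an imaging analysis and not a threat to the trial's primary question.

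**What to change.** Split the ongoing regressor of the prospective memory block into correct match and correct non-match trials. In the event-based task, contrast cues with non-match ongoing trials only; this takes the net repetition weight from -0.36 to 0. If non-matches need no press, use picture onsets, and apply the same onset rule to both sides of the contrast.

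For the time-based task, tabulate from the logs whether each picture at a press was a match or a non-match, and use this to judge whether the pooled comparator is balanced. Report the event-versus-time comparison with a match-balanced comparator as a check. Participant-specific contrast weights are not advised, since each participant gives at most 10 scored presses. Leave the maintenance contrast as it is unless the match share turns out to differ between the ongoing-only and prospective memory blocks.

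The cost is one extra column per prospective memory block and changed contrast weights. No new data are needed. With up to 94 non-match trials left as comparator, the loss of precision is small.

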### Which brain regions are involved in incentive-related processing in general?

Next, we will test which brain regions are associated with incentives in general (i.e., without prospective memory). For first-level analysis, we will define a contrast between incentive and control trials during the anticipation phase of the monetary incentive delay task (i.e., the delay between cue appearance and target appearance). We will include six nuisance regressors for the six movement parameters as well as regressors of physiological data. For second level analysis, we will perform a one-sample t-test on first-level contrast (incentive vs. control) to find out which brain regions are associated with the anticipation of an incentive. Regions that will be identified with this analysis will be used as regions-of-interest (ROI) in subsequent second-level analyses of prospective memory.

### Which brain regions are involved in processing of incentives during prospective memory tasks?

Finally, we will test whether incentive-related processing during prospective memory tasks will be different to incentive-related processing during the monetary incentive delay task. We will first conduct two-sample t-tests on first-level contrast from the first analysis to test whether there are differences in brain activity with an incentive vs. without an incentive for event-based or time-based prospective memory. Next, we will use inclusive masks derived from the ROI analysis using the clusters identified in the monetary incentive delay task. Finally, we will use exclusive masking to test whether additional regions are active during incentive-related processing in prospective memory.

For all neuroimaging analyses, we will set the intensity threshold to *p* < 0.001 uncorrected, and the minimal cluster size threshold *k* to 15 voxels. For small regions (e.g., the hippocampus), we will mask voxels inclusively using generated masks and will set the intensity threshold to *p* < 0.001, uncorrected, with a cluster-size threshold *k* of 3 voxels. This is to reduce Type II errors associated with weak fMRI signal changes in small brain areas.

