### Monetary incentive delay task

To examine the neural substrates of incentive-related processing in the absence of prospective memory, participants will complete a modified version of the monetary incentive delay task [27, 35] that consists of a baseline and an incentive block.

At baseline, the participants will need to respond as fast and correctly as possible to triangles or squares and they will receive feedback (i.e., green tick = correct, red cross = incorrect or too late). Each trial will start with a fixation cross presented in the centre of the screen for 0.6—1.0 s. Then, either of the two stimuli will appear for 0.8 s, followed by another fixation cross (for 1.0—1.4 s) and feedback (for 0.5 s). After 20 trials, the mean response time of all correct answers will be calculated. Next, the incentive block will follow, during which the participants will again respond to triangles or squares (Fig. 3). In contrast to the baseline condition, however, they will be told that for some trials, it would now be possible to keep or lose an incentive. Each trial will start with the presentation of a fixation cross in the centre of the screen for 1—1.5 s, followed by a magnitude incentive cue for 2 s, and another fixation cross for 2—2.5 s. Then, participants will have to respond again to triangles or squares and, after another fixation cross, they will again receive feedback. The magnitude incentive cue will either be an empty white circle indicating a control trial, or a white circle with one horizontal line indicating an incentive trial. The two magnitude incentive cues will be presented 40 times each in randomized order. Hence, participants will complete a total of 80 trials. In order not to lose money, participants will need to answer correctly and faster than their mean response time during baseline. Control trials will be similar to the baseline condition. For incentive trials, answers that were correct and faster as during baseline will be indicated by a centime coin. A lost point (i.e., reaction time was slower than during baseline or an incorrect answer was given) will be indicated by a centime coin with a red cross. Below any 50-cent coin, the cumulative points will be shown. Participants will initially be endowed with an amount of 20 Swiss francs (40 points, each point corresponds to 0.50 Swiss Francs) and will be informed that they may lose it, depending on their response. We will encourage participants to respond as quickly as possible regardless of the type of the incentive cue. Comparable to previous studies, participants will have to keep more than 60% of total points (i.e., 24 points) to finally earn the incentive [27]. Otherwise, they will lose all the money. Again, half of their earnings will be donated to an organization of their choice.

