### Sample size calculation

For the determination of sample size, we used G*power [40]. We based calculations on a previous study that used incentives to enhance event-based prospective memory [12]. The effect size in this study (Cohen’s *f* = 0.25) suggests that an inclusion of *n* = 54 participants would be needed to find such effects in a repeated measures design with two groups and five measurements with *α* = 0.01 and a power of 1-β = 0.99. To account for attrition, drop-out or exclusion due to movement artefacts, we plan to recruit *N* = 60 participants (*n* = 30 in each group).

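### The plan announces a test of whether incentive processing differs between prospective memory and the monetary incentive delay task, but its masking steps never contrast the two effects

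*Protocol article*

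**What the plan says.** In the Protocol article, the section on incentive processing during prospective memory tasks opens with a comparative question: "we will test whether incentive-related processing during prospective memory tasks will be different to incentive-related processing during the monetary incentive delay task". Three steps follow.

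1. Two-sample t-tests between the groups, to "test whether there are differences in brain activity with an incentive vs. without an incentive for event-based or time-based prospective memory".
2. Inclusive masking: "we will use inclusive masks derived from the ROI analysis using the clusters identified in the monetary incentive delay task".
3. Exclusive masking: "we will use exclusive masking to test whether additional regions are active during incentive-related processing in prospective memory".

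The MID map comes from the preceding section, on incentive processing in general: "we will perform a one-sample t-test on first-level contrast (incentive vs. control" trials, in the anticipation phase). That is a within-person contrast.

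The threshold is stated once, for all neuroimaging analyses: "we will set the intensity threshold to *p* < 0.001 uncorrected, and the minimal cluster size threshold *k* to 15 voxels". Small regions use the same p with k = 3. No separate threshold is given for the exclusive mask.

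**The concern.** The only difference tested is incentive group against control group within a PM task. A region that is significant in that map and not in the MID map has not been shown to differ between the tasks, yet the plan describes the step as a test.

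Two features make the problem worse.

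- **The threshold works in reverse for exclusion.** A strict p is cautious for declaring activation but permissive for an exclusive mask. Regions truly active in the MID task that fall short of p < 0.001 stay eligible to be called additional.
- **The maps differ in sensitivity.** The MID contrast is within person, apparently in all participants. The PM contrast is between persons, 30 against 30. Non-overlap is expected even when processing is the same.

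At stake is whether older adults' incentive-related activity is specific to the MID task or generalises to PM, which the Background raises and the Discussion promises to inform.

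**Working it through.** **The plan's own figure.** The article gives no figure for the PM-versus-MID comparison. Its sample size of 54 is behavioural (f = 0.25, two groups, five measurements, α = 0.01, power 0.99). It reproduces for the within-between interaction with an assumed correlation of 0.5: λ = f²·N·m/(1 − ρ) = 0.0625 × 54 × 5/0.5 = 33.75, df 4 and 208, power 0.992. It does not bear on this point.

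**Inputs from the article.**
- Groups: "we plan to recruit *N* = 60 participants (*n* = 30 in each group").
- MID sample: "participants will complete a modified version of the monetary incentive delay task", with no restriction to one group, so n = 60 is taken.
- Voxel threshold: p < 0.001.

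**Assumptions.**
- Equal standardised effect d in both tasks. The article gives no imaging effect size.
- One-sided tests, treated as independent.
- Single voxels; cluster extent is ignored.
- The exclusive mask is cut at p < 0.001.

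**Formulas (noncentral t).**
- MID: df 59, noncentrality d√60, critical t 3.234.
- PM: df 58, noncentrality d√(30/2) = d√15, critical t 3.237.
- Share of PM-significant voxels that miss the mask = 1 − MID power.
- Joint probability of being called additional = PM power × (1 − MID power).

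At d = 0.43 the noncentralities are 3.33 (MID) and 1.67 (PM). The powers are 0.542 and 0.068, so the joint probability is 0.068 × 0.458 = 0.031.

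| d | MID power | PM power | Missed by mask, given PM significant | Joint |
|---|---|---|---|---|
| 0.3 | 0.195 | 0.024 | 81% | 1.9% |
| 0.43 | 0.542 | 0.068 | 46% | 3.1% |
| 0.5 | 0.734 | 0.109 | 27% | 2.9% |
| 0.8 | 0.998 | 0.453 | 0.2% | 0.1% |

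With 54 analysed (27 per group) the joint figures at d = 0.3 and 0.5 are 1.7% and 3.1%.

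**A direct contrast for comparison.** In 200,000 simulated runs with the same raw effect in both tasks, a PM-minus-MID contrast at p < 0.001 declared a difference in 0.07% to 0.09% of runs. Masking called the same voxel additional in 2.9% (d = 0.5, equal SDs). This rose to 25% (PM d = 0.8, MID SD twice as large) and 54% (PM d = 1.0, MID SD three times as large). The SD ratios are assumptions.

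**A liberal mask.** At one-sided p < 0.05, MID power at d = 0.3, 0.43 and 0.5 is 0.743, 0.950 and 0.985. The joint probability falls to 0.024 × 0.257 = 0.6%, 0.068 × 0.050 = 0.3% and 0.109 × 0.015 = 0.2%.

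**Why a difference test inside the surviving clusters does not help.**
1. A survivor must have an observed PM d above 3.237/√15 = 0.836 and, with the p < 0.05 mask, an observed MID d below 1.671/√60 = 0.216.
2. The observed gap is therefore at least 0.62.
3. Its standard error is about √(1/60 + 2/30) = 0.289, or 0.299 with the terms for estimating the SDs. So z is at least 0.62/0.299 = 2.07, already beyond 1.96.
4. Simulation with identical true effects agrees: 100% of selected voxels were significant at 0.05, against about 5% without selection.

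**The case against.** Several points on the other side stand.

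- **Not every region that misses the MID threshold is called additional.** A reader might infer this, but a region must first pass the PM group comparison at p < 0.001 with k = 15.
- **46% is not the rate of mislabelling.** It holds only given PM significance at d = 0.43. The joint figure is about 3.1%, roughly 15 times smaller.
- **The exclusive-mask threshold is inferred.** The article ties only the inclusive masks to the MID clusters. A condensed article may leave mask settings to the fuller plan. The rule for all neuroimaging analyses makes p < 0.001 the natural reading, not an explicit one.
- **The effect sizes are assumed.** Equal standardised effects across a within-person and a between-person contrast is a strong simplification.
- **The third aim does not fall as a whole.** It concerns the correlates of incentive processing during PM, and the unmasked group t-tests address expected activity increases without any mask.
- **The Limitations section concedes part of this.** It says anticipation differs between the tasks and that MID regions may show no PM activation. It does not mention power or false additional regions.

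None of this supplies the missing contrast. The article itself calls the comparison a test, so the gap is in what is stated and not in detail left elsewhere.

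**Conclusion.** The point holds in a limited form. The announced test of a PM-versus-MID difference is not among the listed analyses, and exclusive masking cannot replace it. Under the stated assumptions, a voxel with the same true effect in both tasks would be called additional with probability of about 2% to 3% for d between 0.3 and 0.5, some 20 to 30 times the nominal 0.1%. At d = 0.8 the excess has disappeared. These figures illustrate the mechanism and do not predict the trial's error rate.

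PM power at d = 0.43 is only about 7%, so an empty result inside the inclusive mask is not evidence that MID regions play no part in PM.

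The consequence is confined to the secondary question of specificity or generalisation. The documents do not support extending it to the behavioural primary outcomes or to the unmasked group comparisons.

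**What to change.** 1. Build the exclusive mask from the MID map at a stated liberal threshold, such as p < 0.05 uncorrected. This reduces mislabelling but still tests no difference.
2. Describe the masking as descriptive. Report surviving regions as not shown in the MID task, not as different from it or specific to PM. Do not read an empty inclusive-mask result as absence.
3. If a difference is to be claimed, test the PM group effect against the MID effect on a stated common scale, with a 95% CI. Do this whole-brain or in regions defined independently of both maps, and not inside clusters that the masking selected.

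No new data are needed. Items 1 and 2 are a changed setting and changed wording; item 3 adds one analysis and the choice of a common scale. The price is that fewer regions can be called additional.
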